5. Clinical	Hospital Anxiety and Depression Scale^49^	Parent	Total score	Baseline, 3 months, 6 months
6. Clinical	Insomnia Severity Index^43^	Parent	Total score	
7. Clinical	SleepSuite^34^ (iPad app)	Child	Reaction time (ms) Executive function (accuracy)	Baseline, 3 months
8. Clinical	Health-Related Quality Of Life Measure for Children with Epilepsy^32^ WHO–Five Well-Being Index^50^	Child and parent	Total score Total score	Baseline, 6 months
9. Clinical	Strengths and Difficulties Questionnaire^51^	Child	Total score	Baseline, 3 months, 6 months
10.Clinical	Parenting Self-Agency Measure^52^	Parent	Total score	
11.Clinical	Actigraphy^53^	Child and parent	Total sleep time (min) Sleep latency (min) Sleep efficiency (% asleep of sleep period) All 2-week averages	Baseline, 3 months
12. Clinical	Sickness-related school absences	Child	Total number of days	Randomisation, 3 months, 6 months
13. Health economic	Health utilities derived from: EQ-5D-Y^40^ Child Health Utility Instrument^39^ EQ-5D-5L^54^	Child and parent Child Child Parent	Total score Utility score Utility score Utility score	Baseline, 3 months, 6 months
14. Health economic	Insomnia Severity Index mapped to EQ-5D health state utilities^44^	Parent	Total score Utility score	Baseline, 3 months, 6 months
15. Health economic	Direct costs: National Health Service and Personal Social Services perspective, measured using: Resource Use Questionnaire Case Report Form data PLICS data HES data Serious adverse events (assessed at 3 months, 6 months)	Child	Resource use and total cost	Baseline, 3 months, 6 months, (PLICS and HES at 6 months only)
16. Health economic	Indirect and direct non-medical costs, measured using: Resource Use Questionnaire Case Report Form data	Child and parent	Resource use and total cost	Baseline, 3 months, 6 months
17. Health economic	Cost utility of COSI: societal perspective, using quality-adjusted life years and cost using outcomes 13, 14 and 16	Child and parent	Quality-adjusted life years from the time integral of utility Mean of total costs	Baseline, 3 months, 6 months
Qualitative	Trial experience	Child and parent	Qualitative interview transcript Activity booklet transcript/photos	3 months+3 weeks 6 months+3 weeks

Child measures may be collected by parent proxy.

*Reported as incremental cost per quality-adjusted life year gained.

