### Outcomes and participant timeline

Outcomes are reported in table 1 and were chosen collaboratively by children and young people with epilepsy and their parents, sleep and epilepsy experts^8 17^ in accordance with Core Outcome Measures in Effectiveness Trials guidelines.^30^ Psychometric properties and clinical relevance of outcomes are reported in online supplemental table 3. Each participant will be followed up for 6 months. The participant timeline and estimated time requirement are, respectively, shown in table 4 and online supplemental table 4.

**Table 4 T4:** CASTLE Sleep-E participant timeline and order of outcome completion

	T–4 weeks* Consent and baseline	T0† Randomisation	T+3 months Follow-up visit	T+6 months Follow-up visit
Visit no	1	2	3	4
Informed consent/assent	X			
Review of medical history and EEG results	X			
Eligibility confirmation	X	X		
COVID-19 screener	X		X	
Review of seizure occurrence		X	X	X
Hospital admissions		X	X	X
Demographics	X			
School absences		X	X	X
Check contact details for accuracy		X	X	X
Children’s Sleep Habit Questionnaire^33^	X		X	X
SleepSuite^34^ (iPad)	X		X	
WHO–Five Well-Being Index^50^	X			X
Health-Related Quality Of Life Measure for Children with Epilepsy^55^	X			X
Strengths and Difficulties Questionnaire^51^	X		X	X
CHU-9D/CHU-9D proxy^39^	X		X	X
EQ-5D-Y/EQ-5D-Y proxy^40^	X		X	X
EQ-5D-5L^54^	X		X	X
Parenting Self-Agency Measure^52^	X		X	X
Insomnia Severity Index^43^	X		X	X
Hospital Anxiety and Depression Scale^49^	X		X	X
Resource Use Questionnaire	X		X	X
Knowledge about Sleep in Childhood	X		X	
Randomisation Standard care (SC) or (SC+COSI)^16^		X		
Intervention arm only: COSI^16^				
Actigraphy and sleep diary^53^ (14 days)	X		X	
Confirm continuing trial participation			X	X
Assessment of serious adverse events			X	X
Completion of follow-up Case Report Form			X	X
Review of concomitant medications		X	X	X
Qualitative interview‡			X	X

*Up to 4 weeks flexibility between consent and randomisation to allow delivery of actigraph and iPad.

†Randomisation may be performed once 2 weeks of actigraphy and the minimum dataset are complete.

‡Optional trial component: consenting participants are interviewed within 3 weeks of follow-up visits 3 and 4.

CASTLE, Changing Agendas on Sleep, Treatment and Learning in Epilepsy; CHU-9D, Child Health Utility Index 9D; COSI, CASTLE Online Sleep Intervention; EEG, electroencephalogram.

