### Statistical methods

Statistical analyses of all but health economic and qualitative data will be performed by the trial statistician (LCTC) using SAS software, V.9.4 or later. Intention-to-treat will be the main analysis strategy for primary and secondary outcomes (see table 1 and table 5). Minimisation variables (including seizure frequency, AED and sleep medication details) will be adjusted for at baseline. Statistical significance will be set at the conventional two-sided 5% level; clinical relevance will be based on previous research (see online supplemental table 3). Point estimates with 95% two-sided CIs will be reported adjusted and unadjusted for covariates. No multiplicity adjustments will be made (only one primary clinical outcome, uncorrected secondary outcome analyses).

**Table 5 T5:** Analysis plan for outcome variables in CASTLE Sleep-E (further analyses details are reported in text)

Outcome type	Specific measurement variable	Hypothesis	Method of analysis
Primary			
Clinical	Children’s Sleep Habits Questionnaire^33^	Total score lower in intervention arm at 3 months	Linear mixed effect regression: Fixed effects: intervention (binary) Random effects: trial site (categorical) Covariates: Baseline score Use of sleep medication (binary)
Health economic	Cost* per quality-adjusted life year gained	Not applicable (health economic evaluation)	Cost-effectiveness (utility) analysis
Secondary			
Clinical	Children’s Sleep Habits Questionnaire^33^	Total score lower in intervention arm at 6 months	Linear mixed effect regression (as before)
Clinical	Seizure-free period	Time to first seizure (days) differs between trial arms at 3 and 6 months	Survival analyses Kaplan-Meier curves by trial arm Cox proportional hazards regression (if applicable) Covariates: Use of sleep medication (binary) Trial site (categorical)
Clinical	Time to 6-month seizure remission from randomisation (days)	Time to 6-month seizure remission (days) differs between trial arms at 6 months	Survival analyses (as before)
Clinical	Knowledge about Sleep in Childhood Actigraphy^53^ (2-week average): Total sleep time Sleep latency Sleep efficiency	Total score differs between trial arms at 3 months	Linear mixed-effects regression (as before)
Clinical	Hospital Anxiety and Depression Scale^49^ Insomnia Severity Index^43^	Total score lower in intervention arm at 3 and 6 months	Linear mixed-effects regression (as before)

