Clinical	Sickness-related school absences	Total days differ between trial arms at 3 and 6 months	Poisson mixed-effects regression
Clinical	Health-Related Quality Of Life Measure for Children with Epilepsy^55^ WHO–Five Well-Being Index^50^	Total score differs between trial arms at 6 months	Linear mixed-effects regression (as before)
Clinical	SleepSuite^34^: animal task SleepSuite: bubble task Shape detection Emotion detection Gender detection SleepSuite: maze task	Executive function, reaction time and variability differ between trials arm at 3 months	Poisson/zero-inflated negative binomial regression (depending on presence of overdispersion) 2×2 multivariate repeated-measures analysis of variance Factors: Time (PM/AM)×intervention (pre/post) Fitted per detection task (shape, emotion, gender) Linear mixed-effects regression (as before)
Clinical	Strengths and Difficulties Questionnaire^51^ Parenting Self-Agency Measure^52^	Total score differs between trial arms at 3 and 6 months	Linear mixed-effects regression (as before)
Qualitative	Trial experience†	Not applicable (inductive)	Thematic analysis (interpretive, reflexive and conceptual analytical approach) Discrete sets: intervention/control, child/parent, engagement with intervention/lack thereof, decision-making types, responses/experiences Separately for child and parent, then jointly (dyad) Comparisons with selective objective data as emerging from analysis (eg, anxiety measures, actigraphy)

*Perspective: NHS and PSS perspective; alternative perspective: societal (indirect and direct non-medical costs).

†Source data for trial experience: qualitative interviews (parents and children individually and as dyad), activity booklets (children only).

CASTLE, Changing Agendas on Sleep, Treatment and Learning in Epilepsy; NHS, National Health Service; PSS, Personal Social Services.

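### The school-absence model gives no stated role to the absence value collected at randomisation

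*Protocol article*

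**What the plan says.** Table 1 of the protocol article lists outcome 12, "Sickness-related school absences", with the participant-level metric "Total number of days" and the time points "Randomisation, 3 months, 6 months". Table 4 agrees: the row "School absences" is marked at the randomisation visit and at both follow-up visits.

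Table 5 (Statistical methods) gives the hypothesis as "Total days differ between trial arms at 3 and 6 months" and the method as "Poisson mixed-effects regression". The row names no covariate, offset or random effect.

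Other rows of the same table go further. The primary clinical row lists "Baseline score" and use of sleep medication as covariates, and the later linear rows inherit that set through the tag (as before). The seizure-free row names its own covariates, and the remission row refers back to it. The text adds that minimisation variables will be adjusted for, naming seizure frequency, AED and sleep medication details. It also says that estimates will be reported both adjusted and unadjusted. Absence is not among the variables named.

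**The concern.** No follow-up time has passed at randomisation, so a count of absence days recorded then must describe an earlier period. Children who missed much school before the trial will probably miss more during it, through comorbidity, seizure burden or family and school circumstances. Where that is so, the randomisation value explains part of the spread between children, and a model without it leaves that spread in the error term.

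At stake is the width of the confidence interval for one secondary outcome in a trial of 110 children, with the relevant data already being collected. The primary clinical outcome is not touched.

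**Working it through.** **Figure to reproduce.** None. The article gives no absence rate, variance, target effect or power for this outcome.

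**Inputs from the article.** 110 children allocated 1:1 with 10% attrition (Sample size): 110 × 0.9 = 99, taken as 49 per arm, 98 in all. Two-sided 5% level (Statistical methods).

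**Assumptions not in the article.** Mean of 3 absence days per window; Poisson counts with a lognormal child effect of SD 0.5 or 1.0 on the log scale; correlation of the child effect between baseline and follow-up from 0 to 0.7; 30–65 or 50–65 school days per window; rate ratio 1.0 or 0.6; no site effect. The baseline window was given the same mean count as a follow-up window.

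**What a covariate can remove.** With equal arms and no effect, the variance of the log rate ratio is about (2/n) × [1/μ + (exp(σ²) − 1)].
- σ = 0.5: (2/49) × (0.333 + 0.284) = 0.0252, SE 0.159. The child part is 0.284/0.617 = 46%.
- σ = 1.0: (2/49) × (0.333 + 1.718) = 0.0837, SE 0.289. The child part is 1.718/2.051 = 84%.

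Only the child part can be reduced, so the gain must be larger at σ = 1.0. The formula holds school days constant. The simulated SEs below run slightly higher because school days vary.

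**Simulation.** Between 600 and 1,000 trials per scenario, Poisson regression with robust standard errors, with and without log(baseline days + 0.5). Relative efficiency is (SE without / SE with)², computed before rounding.

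| Child SD | Correlation | Rate ratio | School days | SE without | SE with | Efficiency | Power |
|---|---|---|---|---|---|---|---|
| 1.0 | 0 | 1.0 | 30–65 | 0.291 | 0.292 | 1.00 | – |
| 1.0 | 0.3 | 1.0 | 30–65 | 0.296 | 0.291 | 1.03 | – |
| 1.0 | 0.5 | 1.0 | 30–65 | 0.301 | 0.283 | 1.14 | – |
| 1.0 | 0.7 | 1.0 | 30–65 | 0.305 | 0.266 | 1.31 | – |
| 0.5 | 0.5 | 0.6 | 30–65 | 0.185 | 0.182 | 1.04 | 80.2% to 82.8% |
| 0.5 | 0.7 | 0.6 | 30–65 | 0.177 | 0.170 | 1.08 | 82.7% to 86.5% |
| 1.0 | 0.5 | 0.6 | 30–65 | 0.285 | 0.272 | 1.10 | 48.0% to 50.0% |
| 1.0 | 0.7 | 0.6 | 30–65 | 0.299 | 0.257 | 1.35 | 47.5% to 59.0% |
| 1.0 | 0.5 | 0.6 | 50–65 | 0.305 | 0.283 | 1.16 | 51.8% to 52.7% |

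Over all scenarios run, the efficiency was 0.98–1.03 at correlation 0.3 or below, 1.03–1.16 at 0.5 and 1.08–1.35 at 0.7. At SD 1.0 the robust test rejected a true null in about 8–9% of trials, so the power figures there are slightly high.

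**Second set of assumptions.** Mean 4 days, child SD 0.8, negative binomial fits, 600 trials per scenario. Variance ratios with the baseline covariate were 0.83 and 0.88 at correlation 0.5, and 0.75 and 0.82 at 0.7. The inverses are 1/0.83 = 1.20, 1/0.88 = 1.14, 1/0.75 = 1.33 and 1/0.82 = 1.22. Taking both sets together gives roughly 3–20% at 0.5 and 8–35% at 0.7.

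**School-days offset alone.** Efficiency 1.01–1.09 with 30–65 school days and about 1.01 with 50–65. The second set gave variance ratios of 0.95–1.00, a gain of 0–5%. First recruitment on 30 August 2022, 6 months of follow-up and a planned end on 31 July 2023 imply randomisation up to about the end of January 2023. If the long summer break falls outside that span, the narrow case is the closer one. An offset for days between visits was not simulated.

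**The case against.** The strongest reply is that the row is shorthand. It calls the model mixed-effects without naming a random effect, it is the first Poisson row so it has no earlier Poisson specification to repeat, and the SleepSuite count row lists no covariates either. The covariates of a secondary count model are commonly left to the statistical analysis plan. This stands in part: the article nowhere says that the randomisation value will be left out, so it cannot be said that the trial has decided to ignore it. What remains is that Table 5 does specify covariates for its linear and seizure-free rows, and that the model as stated can be improved with data already collected.

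A second reply is that the randomisation entry may be a weak predictor. No look-back period is given. If it covers only the weeks between consent and randomisation (up to 4), the count carries less information than the simulations assumed. This stands, and is why the low-correlation results belong in the range.

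A reader might infer three stronger points that the documents do not support:
- **Bias from raw totals.** Randomisation balances school-calendar exposure, and both arms have visits at the same nominal 3 and 6 months. Differential visit timing or withdrawal would be needed, and nothing in the article indicates it.
- **Harm to the societal cost analysis.** Table 1 builds outcome 17 from outcomes 13, 14 and 16. The Data collection section takes the costs of school absenteeism from the Resource Use Questionnaire. Covariates in the absence model do not enter that calculation.
- **A need to redefine the outcome per available school day.** Total days over a fixed period is a legitimate outcome. The offset gains only about 0–9%, and needs term calendars that the article does not list as collected.

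**Conclusion.** The point holds as a modest one about precision. Table 5 gives no stated role to the absence value collected at randomisation, although the linear-model rows adjust for their baseline score.

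The gain from using it is about 0–3% in effective sample size at a correlation of 0.3 or below, roughly 3–20% at 0.5 and 8–35% at 0.7. On 98 children, 20% corresponds to about 20 further children and 35% to about 34. These figures rest on assumed means, spread and correlations, on a baseline window comparable to a follow-up window, and on models without a site effect. Differences of a few per cent are within what the simulations can resolve.

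**What to change.** In the statistical analysis plan, before any comparison by arm:

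1. State the look-back period of the absence value recorded at randomisation, taken from the wording of the question that families answer.
2. Add that value as a covariate in the count model, for example as the log of the baseline rate plus a small constant. Keep the unadjusted estimate that the article already promises.
3. Optionally, add log(days between the child's visits) as an offset, from recorded visit dates and matched to the interval that each total covers.

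The covariate leaves the outcome as total days and the comparison as a ratio between arms. The cost is a few lines of analysis-plan text, with no new patient data provided that the look-back period can be established. If it cannot, or differs between children in an unrecorded way, the covariate will be worth less. A school-days offset is not essential. If the plan already contains the covariate, confirming so closes the point.

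### Table 5 sets a Poisson mixed model for school absence days with no overdispersion rule; if trial site is the only random effect, the type I error exceeds 5% whenever the variance exceeds the mean

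*Protocol article*

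**What the plan says.** Table 1 (Introduction) lists "Sickness-related school absences" as secondary clinical outcome 12, with the participant-level metric "Total number of days". The outcome is therefore one count per child per window.

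Table 5 (Statistical methods) states the hypothesis as "Total days differ between trial arms at 3 and 6 months" and the method as "Poisson mixed-effects regression". The row names no random effects, dispersion parameter, robust standard error or alternative distribution. Unlike the linear-model rows, it does not refer back to the primary model.

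Two other entries in Table 5 bear on it. The primary-outcome row specifies "Random effects: trial site (categorical"), the only random effect named anywhere in the table. The SleepSuite row, two rows below the absence row, specifies "Poisson/zero-inflated negative binomial regression (depending on presence of overdispersion").

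The text before the table adds: "Statistical significance will be set at the conventional two-sided 5% level". It also states: "No multiplicity adjustments will be made (only one primary clinical outcome, uncorrected secondary outcome analyses").

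**The concern.** A Poisson model requires the variance to equal the mean once the covariates and random effects are accounted for. Absence days have two features that work against this. Days off sick come in spells, so they are not independent events. Children also differ in how often they are ill; the Introduction itself reports concurrent neurodevelopmental disorders in 35% of these children.

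A random effect for site does not capture either feature, because both act within a site. The confidence interval for the absence rate ratio would then be too narrow, and a few long absences falling by chance in one arm could be reported as a treatment effect. The authors foresaw the problem for one count in Table 5 and wrote a rule for it, but wrote none for this count.

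**Working it through.** **Inputs from the protocol article.** 110 children allocated 1:1, with 10% expected attrition (Sample size); 40 expected sites (Trial setting and eligibility criteria); two-sided 5% level (Statistical methods).

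**Assumed input.** The variance-to-mean ratio of absence days, φ, within site. The documents give no mean, variance or dispersion for this outcome, so results are shown over a range.

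**Step 1: how much can a site effect absorb?** Children analysed: 110 × 0.9 = 99. Per site: 99 / 40 ≈ 2.5. A site intercept shared by two or three children can take up little of the variation between them.

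**Step 2: formula.** If the true variance is φ times the mean and the model assumes φ = 1, the standard error is too small by a factor √φ. The two-sided type I error is then 2 × [1 − Φ(1.96 / √φ)].

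**Step 3: simulation of a site-only Poisson mixed model.** Negative binomial counts with no treatment effect; 98 children (49 per arm); 40 sites; between-site SD 0.2 on the log scale (assumed). The fitted model was Poisson with a random site intercept and a Wald test. Each cell used 500 to 800 runs.

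The plan's own figure comes first: at φ = 1 the formula gives 5.0% and the simulation 4.8% (mean 3 days). The method therefore recovers the nominal level when the Poisson assumption is true.

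| φ (assumed) | √φ | 1.96/√φ | Formula | Simulated, mean 3 days | Simulated, mean 6 days |
|---|---|---|---|---|---|
| 1 | 1.00 | 1.960 | 5.0% | 4.8% | not run |
| 1.5 | 1.22 | 1.600 | 11.0% | 10.8% | not run |
| 2 | 1.41 | 1.386 | 16.6% | 13.1% | not run |
| 4 | 2.00 | 0.980 | 32.7% | 29.0% | 32.8% |
| 5 | 2.24 | 0.877 | 38.1% | not run | not run |

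The Monte Carlo standard error is √[p(1 − p)/runs]: for example √(0.131 × 0.869/720) ≈ 1.3 points at φ = 2, and √(0.290 × 0.710/780) ≈ 1.6 points at φ = 4, mean 3 days. With 15 sites in place of 40, the simulated figure at φ = 1.5 is 9.4%. The site effect removes a little of the inflation, but not most of it.

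**Step 4: does a child-level effect cure it?** The same data (mean 3 days, 40 sites) were refitted with a Poisson model whose random intercept was at child level in place of site. The type I error was 4.8% at φ = 1.5, 5.2% at φ = 2 and 6.9% at φ = 4, with a Monte Carlo standard error of about 1 point. A model with both site and child effects, and a negative binomial mixed model, were not simulated.

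**The case against.** The strongest reply is that the row is incomplete, not wrong. It names no random effects and does not refer back to the primary model. A Poisson model with a child-level intercept is itself a Poisson mixed-effects regression, so the printed words can accommodate a sound analysis. The article is condensed, and an analysis plan exists that is not shown.

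Part of this stands. A reader might infer that the plan makes no allowance for variation between children and that the false-positive rate is several times 5%. The documents support neither as a plain fact. The first depends on the random effects, which the row leaves open. The second depends on a dispersion that they do not report: the formula gives 8% at φ = 1.25, and several times 5% only from about φ = 2 upward. They also give no basis for saying that overdispersion is more certain here than for SleepSuite.

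The reply does not remove the point. Table 5 does go down to overdispersion rules and random effects; it gives one count a rule and not the other, and the only random effect it names is site. Someone following the table as printed would most naturally fit site alone.

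Three further inferences should be resisted:

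- **Costs.** Absences enter an alternative costing scenario, but uncertainty in costs and QALYs is handled by bootstrapping (Health economic evaluation), so these standard errors play no part there.
- **School days.** The lack of a school-days offset does not bias the comparison. The arms are randomised concurrently over the same windows, so holidays balance in expectation, and an article may leave this detail to the analysis plan.
- **Minimisation variables.** Adjustment for them is already stated in Statistical methods.

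**Conclusion.** The point holds conditionally. If site is the only random effect, the test on absence days exceeds its nominal 5% whenever the variance exceeds the mean: about 11% at a ratio of 1.5, 13–17% at 2, 29–33% at 4 and 38% at 5 (the last from the formula only). The lower ends at ratios 2 and 4 come from the simulated mixed model at a mean of 3 days. The ratios are assumptions, and φ means the dispersion left after covariates, so adjusting for strong predictors of absence would lower it.

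The consequence is confined to one secondary outcome. It is tested at 5% without multiplicity correction, so nothing else in the plan would catch a spurious result. The primary CSHQ comparison and the economic evaluation are unaffected. The change is worth making because the safeguard already exists in the same table.

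**What to change.** Change the method in the absence row of Table 5, and the matching analysis plan text, to one of these:

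- negative binomial mixed-effects regression with trial site as a random effect; or
- Poisson mixed-effects regression with a child-level random effect in addition to trial site.

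Either brings the row into line with the overdispersion rule that the table already applies to SleepSuite. If the 3- and 6-month counts are to be fitted in one model, say so and state how the two counts from one child are linked.

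Two additions are optional and would mainly gain precision: an offset of log school days in the window, and adjustment for absences recorded at randomisation, which Table 4 shows are collected.

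The cost is wording, plus wider confidence intervals where overdispersion is present. On the log rate-ratio scale the widening is roughly by √φ: about 1.2 times at a ratio of 1.5, 1.4 times at 2 and 2 times at 4. No new data are needed.

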### Intervention

Participants will be allocated to trial arms (SC or SC+COSI) using minimisation (1:1 ratio). On allocation to SC+COSI, participants will receive an email with access details to COSI. COSI consists of a self-paced, novel, tailored, e-learning package for parents of children with epilepsy that incorporates evidence-based behavioural components. Table 3 provides a brief overview; detailed reports on the development, content and evaluation of COSI have been published.^15 16^ COSI is divided into 13 modules (1 screening for child-specific sleep problems to allow tailoring, 10 content, 1 additional resources, 1 initially hidden evaluation), of which 3 are compulsory (1 screening, 2 content). The non-compulsory modules are recommended based on screening outcome, but all modules are accessible, repeatable and printable. The advice in COSI supports parents to implement general prevention techniques (eg, good sleep hygiene) and specific behavioural change techniques (eg, bedtime fading) relevant to their child’s sleep problems. Three months after first being given access to COSI, parents will be asked by email to complete a COSI evaluation module. At the end of a participant’s trial timeline (6 months), access to COSI will be revoked. After the trial, all families (irrespective of trial allocation) have the option to receive the COSI content in electronic format via email.

**Table 3 T3:** Content of the CASTLE Online Sleep Intervention (COSI)

Module	Module name	Outline content	Compulsory or recommended
A	What is sleep and why is it important	Education about normal sleep physiology and processes	Compulsory
B	Sleep and seizures: a vicious cycle	Information about the relationship between sleep and seizures	Compulsory
C	Personalising this advice for your child	A sleep screening questionnaire to identify key areas of concern or problems around individual child sleep	Compulsory
D	Tips on sleep hygiene for everyone	General advice about key aspects of sleep hygiene	Recommended for all
E	Advanced sleep behaviour training	Introduction to principles of behavioural sleep interventions	Recommended for all
F	Learning difficulties, attention deficit hyperactivity disorder and autism spectrum disorders	Advice for parents of children with other comorbid conditions	Recommended to parents who highlighted (in module C) their child may have comorbid conditions

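### The SleepSuite bubble-task model in Table 5 names no trial-arm factor, so as written it cannot test the between-arm hypothesis in its own row

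*Protocol article*

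**What the plan says.** Table 5 (Statistical methods) states the SleepSuite hypothesis as "Executive function, reaction time and variability differ between trials arm at 3 months". For the bubble task the method is a "2×2 multivariate repeated-measures analysis of variance Factors: Time (PM/AM)×intervention (pre/post"), and it is "Fitted per detection task (shape, emotion, gender"). Table 1 lists the SleepSuite metrics as "Reaction time (ms) Executive function (accuracy"), measured on the child at baseline and 3 months.

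Elsewhere in Table 5, the model for the primary outcome carries "Fixed effects: intervention (binary"), which is the randomised arm. The maze task, in the same row as the bubble task, refers back to that mixed model and so inherits the arm term. The text of Statistical methods adds that "Intention-to-treat will be the main analysis strategy for primary and secondary outcomes (see table 1 and table 5") and that minimisation variables will be adjusted for. Neither statement puts an arm term into the bubble-task model, and no other part of the article does so.

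**The concern.** A two-by-two layout with the levels PM/AM and pre/post is entirely within child. Every child, in either arm, contributes to all four cells, so the layout is complete without any reference to what the child was allocated to. The label is also hard to apply to the control arm, where there is no intervention to be before or after.

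At stake is whether the three bubble tasks (shape, emotion, gender) yield a randomised comparison at all. If the entry is followed literally, the analysis has no arm contrast to report against the stated hypothesis. The one effect that responds to COSI, the pre/post main effect, also responds to anything else that changes over three months in both arms. Repeating the same game and being three months older are plausible sources of such change, although the documents give no figure for either.

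**Working it through.** The documents state no power, effect size or sample size for SleepSuite, so there is no figure of theirs to reproduce. The check has two parts.

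**1. What the stated model can estimate**

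| Effect in the stated model | What it contrasts | Compares SC+COSI with SC? |
|---|---|---|
| PM/AM | evening with morning, same children | No |
| Pre/post | 3 months with baseline, same children | No |
| PM/AM × pre/post | change in the evening with change in the morning | No |

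Let the mean change be *s* in SC and *s + e* in SC+COSI, where *e* is the arm effect. With 1:1 allocation and both arms analysed, the pooled pre/post effect is

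½·*s* + ½·(*s* + *e*) = *s* + *e*/2.

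One number estimates a sum of two unknowns, so *e* cannot be recovered from it.

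**2. How much this could matter (illustration)**

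Inputs from the article: two-sided 5% level; 110 children, 1:1; 10% attrition, hence 55 × 0.9 = 49.5, taken as 49 per arm (98 in all).

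Assumptions, not in the article: a single outcome with SD 1, four sessions per child (PM and AM at baseline and at 3 months), and correlation 0.6 between any two sessions of a child.

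- Variance of a two-session mean: (1 + 0.6)/2 = 0.8.
- Variance of a child's change (3-month mean minus baseline mean): 0.8 + 0.8 − 2 × 0.6 = 0.4.
- Standard error of the pooled pre/post effect: √(0.4/98) = 0.0639.

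With no arm effect, the chance that the pre/post test is significant depends on *s*/0.0639:

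| Shared change *s* (SD) | *s*/SE | Pre/post test significant (10,000 simulated trials) | Exact (non-central t, 97 df) |
|---|---|---|---|
| 0 | 0 | 5.0% | 5% |
| 0.1 | 1.57 | 34% | 34% |
| 0.2 | 3.13 | 88% | 87% |
| 0.3 | 4.70 | 99.7% | 99.6% |

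In the same simulations, and also at a shared change of 0.5 SD, two tests that include arm rejected in 4.4% to 5.2% of trials. These were arm × pre/post and a baseline-adjusted comparison of the arms.

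The error can also run the other way. Take a true arm effect of 0.5 SD and a shared change of −0.25 SD. The pooled effect is −0.25 + 0.5/2 = 0, and the pre/post test was significant in 3.4% of trials.

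With arm in the model, the same 0.5 SD effect is found as follows:

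- Arm × pre/post: standard error √(2 × 0.4/49) = 0.128; 0.5/0.128 = 3.91; power about 97%.
- Baseline-adjusted: residual variance 0.8 − 0.6²/0.8 = 0.35; standard error √(2 × 0.35/49) = 0.120; 0.5/0.120 ≈ 4.18; power about 98%.

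The PM/AM × pre/post interaction rejected about 5% of the time in every scenario. It carries no information about an arm effect that is equal in both sessions.

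**The case against.** The best reply is that the entry is mislabelled and not a settled analysis. Intervention means arm elsewhere in Table 5. If it does here, the layout is PM/AM by arm at 3 months, which fits the hypothesis, and pre/post is a slip. Alternatively, the two-by-two may describe only the within-child part, with arm left implicit. The table does leave arm unstated in other entries: the Cox model lists only sleep medication and site as covariates, and the Poisson model for school absences lists no terms. Either reading is possible and neither is stated. This entry differs from those others because it writes out both factors and their levels, and those levels exclude arm. So the reply limits what can be said about the authors' intention, but the text still needs correcting.

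A reader might infer three stronger points, and the documents do not support them.

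- *That improvement over time would be credited to COSI.* Nothing says that a pooled pre/post change will be reported as a COSI effect; the row's hypothesis is explicitly between arms. What is shown is that the model does not answer its hypothesis.
- *That the pre/post effect measures only practice and maturation.* It also carries half of any arm effect.
- *That children with a missing session would be dropped, in conflict with intention-to-treat.* Handling of missing secondary-outcome sessions is commonly left to the statistical analysis plan, which is not shown. Excluding incomplete cases does not by itself contradict analysis by allocated arm.

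It is also fair that the size of the problem is hypothetical, because no practice effect or retest correlation is given.

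**Conclusion.** The point holds as an internal contradiction. The factor structure fixed for the bubble task has no randomised comparison, while its hypothesis is one. This is not detail that an article leaves out for brevity, because the structure is stated and does not fit.

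The algebra (*s* + *e*/2) needs only 1:1 allocation and both arms in the analysis. The 34% to over 99% range rests on the assumed shared changes of 0.1 to 0.3 SD, the correlation of 0.6 and a single outcome in place of the multivariate response; with no shared change the rate is the nominal 5%. It shows how sensitive the pre/post test is to shared change and does not predict what this trial will find.

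The reach is limited to three detection tasks within one secondary outcome. The primary outcome, its model and the sample size are untouched. The entry should be corrected before analysis, but it does not threaten the trial's main conclusion.

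**What to change.** In Table 5, and in the statistical analysis plan if it repeats this entry, do one of the following for each detection task.

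- Keep the repeated-measures analysis, add trial arm (SC versus SC+COSI) as a between-child factor, and name arm × pre/post, averaged over PM and AM, as the test.
- Or model the 3-month PM and AM scores on arm, adjusted for the corresponding baseline score, with PM/AM as a within-child factor. Name the arm contrast averaged over PM and AM as the test. If an arm × PM/AM term is included, the averaged contrast must be stated, because the arm coefficient alone would then depend on the coding.

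If pre/post was meant to read as arm, correct the label and say how the baseline score enters.

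The cost is a few words in one table entry. The data, visits and software stay the same.
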